## 8. HANDLING AND STORAGE OF ORGANIC SAMPLES (if applicable)

Not applicable

## 9. DATA MANAGEMENT AND PROCEDURES TO ENSURE DATA CONFIDENTIALITY

The Promoter agrees to comply with the Privacy Laws (as defined below), including those areas relating to security measures and confidentiality. The Promoter warrants, on his own behalf and on behalf of the Investigator, to be fully aware of all obligations arising from any applicable legislation relating to medical professional secrecy and the protection of patients' personal data, including but not limited to the EU Regulation 2016/679, the Privacy Code (D.Lgs 196/03, s.m.i), the provisions, guidelines and general authorisations of the Italian Data Protection Authority (collectively "Privacy Laws").

The Promoter undertakes that all its personnel involved in the conduct of the study will comply with the Privacy Laws and the Promoter's instructions regarding the protection of personal data, including aspects of data security and confidentiality. This obligation includes, for example: (i) providing the patient involved in the study with a complete privacy policy in accordance with the law (in particular, EU Regulation 2016/679, Legislative Decree 196/2003 as amended, as well as the above-mentioned Guidelines of 24 July 2008); (ii) obtaining the patient's written informed consent prior to his/her participation in the study; (iii) respecting the privacy rights of each data subject as established by the applicable Privacy Laws; (iv) taking all appropriate physical, logical, organisational, technical and IT measures in compliance with the applicable Privacy Laws.

Due to the particular sensitivity of the data processed in the firm, specific technical measures have been adopted to increase the level of data security, without prejudice to any other minimum measures. This, with particular reference to the operations of recording with electronic and/or paper instruments the data of the persons involved in the study at the test centre, to their transfer by telematic means to subjects who carry out, on behalf of the latter, the validation and statistical processing of the data, as well as the management of the same database. In connection with these processing operations, the promoter has taken appropriate measures to ensure the protection of the recorded data from the risks of unauthorised access, theft or partial or total loss of the paper documents, storage media or portable or fixed processing systems.

A username and password are required to access the computers where data is entered. In addition, access to the database in order to start a data entry session is protected by username and password.

The following precautionary measures are taken to guarantee data confidentiality and to prevent data manipulation and loss:

- Access to the data is restricted to authorised members only. Authorised members are: Researcher in charge of research, Principal Investigator, examining physician.
- The network is protected by firewalls
- The Internet connection is encrypted with a digital certificate (SSL technology)
- The database is located on a server, protected by a password that is changed periodically.
- Access to the database is password protected and is only accessible to the persons responsible for the centre.
- Regular back-ups are performed.

Paper materials relating to clinical evaluations will be stored in cabinets, the keys to which will only be in the possession of persons authorised by the persons in charge of the study site.

The promoter has adopted a centralised database at the promoter or others who perform the subsequent validation and statistical processing of the data.

The promoter guarantees that it will require the adoption of secure communication protocols for the transmission of any paper documentation.

Finally, it is specified that with specific reference to the database, suitable authentication and authorisation systems are adopted for the persons in charge according to the roles and requirements of access and processing and suitable procedures for the periodic verification of the quality and consistency of the authentication credentials and authorisation profiles assigned to the persons in charge of processing.

The Investigator will appropriately disassociate patient identification data from the data relating to the results of the trial (e.g. by anonymising such data by identifying the results with a randomly generated alphanumeric code) so that only pseudo-anonymised data will be processed by the Promoter.

The Promoter will allow access to clinical data (including medical records) and any other information that may be relevant to the study, always in accordance with applicable Privacy Laws and respecting the security measures and confidentiality of the data.

Within the limits of the information provided to the patients of the trial, the personal data of these subjects will be accessible only to employees, collaborators, monitors and auditors of the Promoter, and/or by the competent authorities in the exercise of their functions.

The Promoter and the Investigator undertake to inform each trial patient clearly and completely about the way in which their personal data will be processed prior to their participation in the trial, in accordance with the applicable Privacy Laws.

Prior to the acquisition of the data, the Investigator agrees to make appropriate disclosures to each patient regarding the nature, purpose, results, consequences and risks of the study prior to that patient's participation in the study. Prior to the patient's enrolment, the Investigator or his authorised delegate will obtain in writing the patient's informed consent: (a) to participate in the study; (b) to the communication of the relevant confidential information; (c) to the processing of personal data; (d) to the transfer of the documentation containing the patient's personal data, including sensitive health data, to the Promoter and/or to the competent authorities and/or to other institutions, including those outside the European Union, in compliance with the laws and in accordance with the applicable Privacy Laws.

The Promoter undertakes to keep the original paper documentation (e.g. informed consent) for at least 7 years in compliance with dl 200/2007.

## 10. STUDY DURATION

Total duration of the study: 24 months (including data analysis)

This project includes three consecutive phases, for 6 work packages (WP) integrated to deliver our stated objectives over the project's lifetime. During the first 9 months of the project, Unit 1 and Unit 2 will recruit patients and HC, collect clinical and demographic data according to the project protocols, collect and develop behavioral, neurophysiological, and MRI biomarkers. MRI scans will be obtained from the Unit 1 and 2 and sent to Unit 3 for analysis (WP1, WP2). From 10 to 12 months, the behavioral, neurophysiological, and MRI biomarkers will be combined and processed separately by means of a data mining approach (XAI analysis) to develop a computational paradigm aiming at better defining their diagnostic value and then to validate them for Unit 1 and 2 (WP3). From 13 to 22 months, Unit 1 and 2 will assess the resulting biomarkers identified in the diagnostic biomarker algorithm (experiment 1) in FMD in a cohort of patients with "organic" motor disorders (weakness due to peripheral neuromuscular disorders, essential tremor, and idiopathic adult-onset dystonia); and the Unit 1 will evaluate the possible modulation of the diagnostic biomarker algorithm (experiment 1) before and after rehabilitation and clinical improvement of functional motor and NMSs symptoms. Unit 3 will provide MRI biomarkers for patients with "organic" motor disorders (WP4) and analyze task-based fMRI before and after rehabilitation (WP5). From 23 to 24 months, we will analyze, disseminate, and communicate the final data (WP6). Dissemination and communication (WP 6) will include the project's visual identity (logo, packaging, website, and even your email templates), public website, leaflets and flyers, social media, videos, and press releases. Dissemination activities will maximize the impact of research results in the public domain, such as the scientific community, stakeholders, policymakers, through an open science framework and patient's charity. Primary and secondary results will be exploited and disseminated through scientific papers, conferences, talks, workshops.

## 11. SAMPLE SIZE CALCULATION

Sample size calculations are based on the simulations performed by Guo et al. 2010 (26). We will use Random Forests (RF) owing to their non-parametric nature that contributes to robust performance under settings of varying class conditional biomarkers distributions. Assuming a skewed distribution of the dataset and up to 100 neurophysiological and imaging features to include in the statistical analysis,  $k=1\%$  (where  $k$  is the percentage of biomarkers among  $n$  features measured per subject) and effect size for each biomarker  $< 0.3$ , we need a sample size of 150 subjects (75 patients with FMD and 75 HC, among all Units) using RF that ensures a statistical power  $>90\%$ , with a 4-fold cross-validation process. **To address concerns regarding the**

validity of cross-validation-based estimates in relatively small samples, we will pursue an additional external validation based on an independent test set of 150 subjects (75 patients with FMDs and 75 HC, among all Units). Finally, the diagnostic biomarker algorithm (experiment 1) will be tested against a population of patients of 150 patients with "organic" motor disorders of similar sample size (50 with weakness due to muscle diseases, 50 with ET, and 50 with dystonia, among all Units). Based on our previous study, for the rehabilitative study Unit 1 will enroll 34 patients, assuming  $\alpha = 0.05$ , power 90%, and T0-T1 rehabilitation effect size of 0.605 (mean difference 5.52; Standard deviation 9.11) on the primary outcome (SFMDRS) and a drop-out rate of 10%(8).

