### **3. PROJECT AIMS**

#### **Specific aim 1**

To develop a biomarker-based diagnostic algorithm for FMD by modeling behavioral, neurophysiological, and MRI biomarkers to investigate the motor, exteroceptive and interoceptive domains. Deep learning will be used, and visualization and interpretability methods will be exploited to identify the most sensitive measures. The results obtained will determine which biomarkers are the hallmarks for FMD diagnosis identifying the key differences between FMD and healthy controls.

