#### **Specific aim 3**

To explore whether the validated biomarkers change after a multidisciplinary rehabilitation training and correlate them with changes in quality of life and motor and non-motor symptoms of FMD patients to determine their potential role in measuring treatment response and giving prognostic information.

We hypothesize that a composite panel of clinical, neurophysiological, and neuroimaging biomarkers covering motor, exteroceptive and interoceptive domains would be instructive in the diagnosis and prognosis of FMD from the earliest symptoms onset. It would allow the correct diagnosis of these patients early and delineate specific management pathways for future intervention trials with positive socio-economic impact.

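### Protocol section 11: power above 90% with 75 + 75 subjects does not follow from the stated inputs, because the effect size is bounded only from above and its metric, the alpha and the power criterion are not given

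*Protocol*

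**What the plan says.** Protocol section 11 takes the size of the first data set from a published simulation study: "Sample size calculations are based on the simulations performed by" a cited source that is not reproduced. The inputs it lists are:

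- skewed data, with no form given;
- "up to 100 neurophysiological and imaging features to include in the statistical analysis";
- k = 1%, where k "is the percentage of biomarkers among" the features measured on each subject;
- an "effect size for each biomarker" below 0.3;
- a random forest with 4-fold cross-validation.

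From these it concludes that 150 subjects suffice: "75 patients with FMD and 75 HC, among all Units) using RF that ensures a statistical power" above 90%. A further 75 + 75 subjects form an independent test set, which the section justifies by doubts about cross-validation in small samples. The power figure does not cover that set.

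Two other places bear on the assumptions. Specific aim 3 states the working hypothesis: "We hypothesize that a composite panel of clinical, neurophysiological, and neuroimaging biomarkers covering motor, exteroceptive and interoceptive domains" would help in diagnosis and prognosis. Specific aim 1 names a different model class: "Deep learning will be used, and visualization and interpretability methods will be exploited to identify the most sensitive measures".

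**The concern.** A power statement needs an effect at least as large as some stated value. Section 11 gives a value that the effect stays below. Power falls as the effect shrinks, so the assumption admits scenarios with almost no power, and the calculation cannot promise 90%.

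The sentence also lacks three items needed to check it: the effect-size metric, the alpha, and what counts as success (accuracy above chance, or picking out the true biomarker). The scenario contains at most one informative feature, while the hypothesis concerns a panel across several domains.

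This sentence is the only justification given for the size of the first 150 subjects. If the assurance of more than 90% is taken at face value, a weak or unstable algorithm will be hard to interpret: nobody could say from the protocol what size of signal the study was able to find.

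**Working it through.** **Inputs from section 11:** 75 FMD and 75 HC; up to 100 features; k = 1%; effect below 0.3; claimed power above 90%.

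**Assumed, because not stated:** two-sided alpha 0.05, with one-sided 0.05 and 0.05/100 = 0.0005 as variants.

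**Step 1. Number of informative features.** 0.01 × 100 = 1, so at most one.

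**Step 2. Reproducing the figure.** The metric, alpha and success criterion are missing and the cited simulations are not at hand, so the figure cannot be reproduced. The only effect size whose construction the section shows is in the rehabilitation sub-study: 5.52/9.11 = 0.606, given as 0.605. That is a standardised mean difference, so 0.3 is first read as d on normal data.

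**Step 3. Power for one known feature, d = 0.3.** Power ≈ Φ(d√(n/2) − z), with √(75/2) = 6.124 and 0.3 × 6.124 = 1.837.

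- Two-sided 0.05: Φ(1.837 − 1.960) = 0.451 (0.446 with the t distribution).
- One-sided 0.05: Φ(1.837 − 1.645) = 0.576.
- 0.05/100: Φ(1.837 − 3.481) = 0.050.

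At smaller effects, which the assumption also allows, two-sided power is about 23% at d = 0.2 and 9% at d = 0.1.

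**Step 4. What 90% would need.**

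- With 75 per group, d = (1.960 + 1.282)/6.124 = 0.53. At 0.05/100, d = (3.481 + 1.282)/6.124 = 0.78 (0.79 with the t distribution).
- With d = 0.3, n = 2(1.960 + 1.282)²/0.09, or 234 per group (235 with the t distribution).

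**Step 5. Accuracy criterion, normal data, d = 0.3.** The best possible accuracy is Φ(0.15) = 0.560, and the AUC is Φ(0.3/√2) = 0.584. A one-sided exact binomial test against 50% in 150 subjects needs at least 86 correct (actual alpha 4.3%). With true accuracy 0.560, the chance of reaching 86 is 0.40.

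**Step 6. Other metrics, taken at the 0.3 limit.**

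| 0.3 read as | Equivalent d | Power, known feature, two-sided 0.05 | Power at 0.05/100 |
|---|---|---|---|
| d | 0.30 | 0.451 | 0.050 |
| f (d = 2f) | 0.60 | 0.957 | 0.577 |
| r (d = 2r/√(1 − r²)) | 0.63 | 0.971 | 0.645 |
| f² (d = 2√f²) | 1.10 | >0.99 | >0.99 |
| η² (d = 2√(η²/(1 − η²))) | 1.31 | >0.99 | >0.99 |

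The upper-bound problem remains even on a favourable metric. For example, f² = 0.05 satisfies the assumption and gives d = 2√0.05 = 0.447, and Φ(0.447 × 6.124 − 1.960) = 0.78.

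**Step 7. Skewed data, d = 0.3.** For an exponential distribution shifted by 0.3 SD, the ideal rule has accuracy (1 + 1 − e^(−0.3))/2 = 0.63 and passes the same 86/150 test with probability about 93%. For a shifted lognormal (sigma 1) the figures are 69% and above 99%. With milder skew (gamma shape 2 or 4, lognormal sigma 0.5) power is 47% to 61%.

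**Step 8. Small random forest simulations** (100 features, one informative, 4-fold cross-validation, 60 to 80 runs). At d = 0.3 the forest reached 86/150 in 10% of runs with normal data and 30% with shifted-exponential data. The true feature ranked first in 10% and 84% of runs respectively. These figures are only indicative: the runs are few, and with normal data and no effect the accuracy test passed in 15% of runs.

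**The case against.** The strongest reply is that the figure comes from published simulations with their own definitions, and that the protocol assumes skewed data. Much of this stands. Steps 6 to 8 show that the result depends heavily on the metric, the skew and the success criterion. A reader might infer from the figures for normal data that 75 + 75 cannot reach 90% even with a perfect rule. The documents do not support that: a strongly skewed feature with d = 0.3, or an f² or η² reading, can give more than 90% at the limit. Nor do they show that the cited simulations were misread.

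Three further points are fair.

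- Planning on one informative feature can be a deliberately hard case. It does not contradict the panel hypothesis; it only leaves the calculation without a scenario that matches it.
- The second 75 + 75 subjects have their own rationale, so it would be wrong to say that both data sets rest on this figure.
- Section 11 commits to random forests, and section 6 names tree-based and instance-based classifiers with random forest feature importance. The mentions of deep learning mean only that the power figure does not extend to other models. Which model should be primary is a separate choice.

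None of this repairs the upper bound. Whatever the metric, alpha or criterion, an effect that may be close to zero does not assure 90% power.

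**Conclusion.** The point holds in a conditional form. The claim of more than 90% power does not follow from what section 11 states, because the effect size has no lower limit and the metric, alpha and success criterion are absent. That conclusion needs no outside source.

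The size of the shortfall does rest on assumptions. If 0.3 is a standardised mean difference and the data are near normal, power is about 45% for one known feature, about 5% at 0.05/100, and about 40% for an ideal rule tested against chance. On other metrics or with strong skew, power at the limit may exceed 90%. The figure is therefore unsupported as written, and not shown to be wrong on the cited simulations' own definitions.

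**What to change.** In section 11, remove the assurance of more than 90% power and do one of the following.

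1. Restate what 75 + 75 delivers, giving a minimum effect size per biomarker with its metric, the form of the skewed distribution, alpha, the success criterion (accuracy above chance or selection of the biomarker), and a number of informative features in line with the hypothesised panel. If the one-feature case is kept as a conservative scenario, say so.
2. Replace the power figure with the precision of the held-out estimates. For 80% sensitivity in 75 patients, the 95% interval is about ±1.96 × √(0.8 × 0.2/75) = ±0.09, or 9 percentage points.

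In the first case, add that the figure applies to the random forest only.

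The cost is a rewritten paragraph and, for the first option, a short simulation. No extra patients are needed. The stated figure may become less favourable.

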## **2. EXPERIMENTAL DESIGN**

### **Experimental study without drug or medical device**

#### **Experimental design aim 1**

This is a cross-sectional study that will involve 150 patients with a clinically definite diagnosis of FMD based on Gupta and Lang diagnostic criteria (1) and 150 matched HC consecutively recruited by Unit 1 (75 patients and 75 HC) and Unit 2 (75 patients and 75 HC) (WP1). Healthy controls, matched for age and sex, will be recruited through public advertisements. We will develop behavioral, neurophysiological, and MRI biomarkers for each patient and HC in the motor, exteroceptive, interoceptive and cerebral domains (see methods, data collection section). Unit 1 and 2 will perform the same behavioral, neurophysiological, and MRI tests on FMD and HC. 3T MRI data will be processed by Unit 3 to estimate brain structural and functional MRI features of sensorimotor and non-motor networks (WP2). The diagnostic biomarker algorithm through eXplainable Artificial Intelligence (XAI) methods will be developed by Unit 2 (WP3).

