### **4. SUBJECTS**

#### **Experimental design 1.**

150 patients with a clinically definite diagnosis of FMD based on Gupta and Lang diagnostic criteria (1) and 150 matched HC consecutively recruited by Unit 1 (75 patients and 75 HC) and Unit 2 (75 patients and 75 HC) (WP1).

Inclusion criteria for patients will be age higher or equal to 18 years and a clinically definite diagnosis of FMD (1). Exclusion criteria for patients will be Mini-Mental State Examination score lower or equal to 24; physical impairment precluding signing the informed consent for participation; certified neurological and/or psychiatric comorbidities (i.e., neuropathy, seizures, major depression); contraindications for 3T MRI.

Inclusion criteria for HC will be age higher or equal to 18 years; Exclusion criteria for HC will be Mini-Mental State Examination score lower or equal to 24; physical impairment precluding signing the informed consent for participation; certified neurological and/or psychiatric comorbidities (i.e., neuropathy, seizures, major depression); contraindications for 3T MRI.

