## 12. STATISTICAL ANALYSIS

eXplainable AI (XAI) analysis. First, ad-hoc models will be identified based on the available data, accounting for type (multi- modal), numerosity, completeness (missing data). Then, the models will be trained and validated following k-fold cross- validation and finally tested on a new (unseen) set of data to assess their generalization properties. Classical linear methods that are the most widespread in the clinical field will be used for benchmarking. Finally, we will apply XAI methods for assessing feature relevance, and consensus will be assessed under the assumption that this will provide information about the robustness of the outcomes (27-29). This will also be investigated through association studies with parameters holding clinical relevance.

Firstly, we will employ XAI analysis using the dataset from the first recruited 150 subjects (75 FMD and 75 HC). Secondly, external validation will be performed on an independent dataset of features collected on an additional sample of 150 subjects (75 FMD and 75 HC). Finally, the biomarkers identified in the diagnostic biomarker algorithm (experiment 1) will be tested against patients with organic neurological disorders recruited by Unit 1 and 2.

For the rehabilitation sub-study, descriptive statistics will include frequency tables for categorical variables and mean and standard deviation for continuous variables. The normality of data distribution will be checked with the Shapiro-Wilk test. Parametric (paired t-test) or non-parametric tests (Wilcoxon test) will be applied accordingly to compare the means for the two-time points (T0, T1). fMRI data will be analyzed using the SPM12 software. One-sample t tests will be used to evaluate significant mean brain activations during the task. Changes over time will be evaluated using a paired t test. All the longitudinal data deriving from the rehabilitation sub-study will be handled with a complex approach named Gaussian Process Panel Modeling (GPPM). GPPM provides great flexibility because of the large number of models it can represent. It allows classical statistical inference as well as machine learning inspired predictive modeling, with the advantage of obtaining person-specific predictions of treatment response (30).

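### The second 150 subjects give a temporal, not an external, validation, and the recruitment-order split leaves Unit free to be associated with diagnosis in opposite directions in the two halves

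*Protocol*

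**What the plan says.** Section 2 (aim 1) and section 4 give the cohort: 150 FMD and 150 HC, "consecutively recruited by Unit 1 (75 patients and 75 HC) and Unit 2 (75 patients and 75 HC) (WP1". Section 2 has controls matched on age and sex and recruited through public advertisements; Unit is not named as a matching factor. Section 10 puts all of this recruitment, by Units 1 and 2, in the first nine months.

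Section 11 sizes the development set: "we need a sample size of 150 subjects (75 patients with FMD and 75 HC, among all Units". To meet a worry about cross-validation in fairly small samples, it adds "an additional external validation based on an independent test set of 150 subjects (75 patients with FMDs and 75 HC, among all Units".

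Section 12 gives the rule that separates the two sets. For development: "we will employ XAI analysis using the dataset from the first recruited 150 subjects (75 FMD and 75 HC". For test: "external validation will be performed on an independent dataset of features collected on an additional sample of 150 subjects (75 FMD and 75 HC". It says that testing on unseen data is meant to assess generalization. No section states how many FMD or HC from each Unit belong in each half.

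On imaging, section 10 says "MRI scans will be obtained from the Unit 1 and 2 and sent to Unit 3 for analysis", whereas section 6 (Experimental design 1) places the scans in Verona.

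**The concern.** There are two linked problems.

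The first is the label. A reader of the results will take an external validation to mean performance at a site that played no part in building the model. Here both sets are drawn from both Units, under one protocol, in one recruitment period. The test subjects are new; the setting is not.

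The second is the split rule. A development set defined by recruitment order that must also hold 75 FMD and 75 HC means, in practice, the first 75 of each group. Those groups accrue separately: patients come consecutively from clinic, controls from advertisements. If one Unit is relatively quicker with patients and the other with controls, Unit is associated with diagnosis in the development half. Because each Unit's total is fixed at 75 + 75, the opposite association then falls in the test half. A feature that differs between Units for technical reasons could be ranked as a biomarker, and experiments 2 and 3 carry forward the biomarkers selected in experiment 1.

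**Working it through.** **Inputs.** Unit totals are 75 FMD + 75 HC each (sections 2 and 4). The halves are 75 FMD + 75 HC each, both from all Units (section 11). The split is by recruitment order (section 12). Recruitment takes place at Units 1 and 2 only, in months 1 to 9 (section 10).

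**Step 1: the plan's own sizes.** Each Unit gives 75 + 75 = 150, so two Units give 300, and the halves are 150 and 150. The stated figures reproduce.

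**Step 2: what the test set can show.**

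| | Development set | Test set |
|---|---|---|
| Subjects | first 150 | a further 150, no overlap |
| Units | 1 and 2 | 1 and 2 |
| Test procedures | the same | the same |
| Recruitment period | months 1–9, earlier part | months 1–9, later part |

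Only the subjects and the calendar order differ. That is a temporal validation over a short interval.

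**Step 3: a rule that sees only Unit.** Let f FMD and h HC from Unit 1 fall in the development half, and classify everyone from Unit 1 as FMD.

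- Development: correct = f + (75 − h), so accuracy = 50% + (f − h)/150.
- Test: Unit 1 now contributes 75 − f FMD and 75 − h HC. Correct = (75 − f) + h, so accuracy = 50% − (f − h)/150.

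If f < h the better rule in development is the mirror image, so in general the accuracies are 50% + |f − h|/150 and 50% − |f − h|/150.

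The protocol gives no recruitment rates, so the values of f and h below are assumptions chosen to show the range:

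| f / h | Development | Test |
|---|---|---|
| 50 / 50 | 50.0% | 50.0% |
| 38 / 37 | 50.7% | 49.3% |
| 45 / 30 | 60.0% | 40.0% |
| 50 / 25 | 66.7% | 33.3% |

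The first row shows that a faster Unit does no harm in itself. What matters is a difference between f and h.

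**Step 4: if Unit order is random in each group.** Then f and h are independent hypergeometric counts (75 drawn from 150, of whom 75 are from Unit 1). Each has variance 75 × ½ × ½ × 75/149 = 9.44, so f − h has SD √18.88 = 4.34. The normal approximation to the mean of |f − h| is 0.798 × 4.34 = 3.47. Simulation with 200,000 draws gave a mean of 3.45 and a 95th percentile of 9.

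- Mean: 50% + 3.45/150 = 52.3% in development, 47.7% in test.
- 95th percentile: 50% + 9/150 = 56% in development, 44% in test.

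**Step 5: the split taken within Unit and diagnosis.** Take the first 38 FMD and 38 HC from one Unit, and the first 37 FMD and 37 HC from the other. Development is then 75 + 75, and the test set is 37 + 38 = 75 of each group. Now f = h, so the Unit-only rule scores 50% in both halves.

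**Step 6: precision.** For an assumed sensitivity of 0.80, the 95% half-width with 75 FMD is 1.96 × √(0.8 × 0.2/75) = 9.1 points, unchanged by the new split. By Unit, with 37 FMD, it is 1.96 × √(0.16/37) = 12.9 points, so results by Unit are descriptive.

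**The case against.** **The test set serves its stated purpose.** Section 11 adds the second sample because of doubts about cross-validation, and a later, non-overlapping sample answers that. Section 10 speaks of validation for Units 1 and 2, and no section expressly claims transfer elsewhere. This stands. The remaining point is the word external and what will be read into it.

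**The confounding is hypothetical.** This also stands. Matched controls recruited alongside patients within each Unit would keep f close to h. A reader might infer that the plan builds site confounding in. The documents do not support that: they give no accrual rates, and Unit and diagnosis are balanced over all 300.

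**The harm runs in one direction.** A reader might also infer that a site signature could produce a falsely good validation. It could not do so by this route: the association reverses in the test half, so it pulls test accuracy down. Nor do the Unit-only figures measure the distortion in a Random Forest with up to 100 features.

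**Balance by Unit could be left to an SAP, and section 13 acknowledges heterogeneity and imbalance.** In part. But sections 11 and 12 already fix the rule as recruitment order and fix the label, and section 13 names families of methods without tying any to the split.

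**A split by Unit is the obvious remedy.** Training on one Unit and testing on the other keeps 150/150 and is tempting as a replacement. It is a trade-off: swapping gives two models where aims 2 and 3 need one; training on Unit 1 puts all 34 rehabilitation patients in the development data; and training at two sites is lost. Unit 2 also shares the protocol, the recruitment period and central MRI processing, so one held-out Unit would be only a limited test of transfer.

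**Conclusion.** The concern holds in two limited parts. First, the second 150 subjects give a temporal validation; calling it external claims more than the design can show. This rests on the text alone. Second, the split rule permits an association between Unit and diagnosis in development, mirrored in test. This part is conditional: it needs the Units to recruit FMD and HC at different relative speeds, the first 75 of each group to form the development set, and each Unit to reach its 75 + 75. The size ranges from a few points by chance to ten points either side of 50% under the assumed 45/30. The likely damage is to feature ranking and cross-validated accuracy, with test accuracy lowered for a reason unrelated to the biomarkers. Whether scanner effects can contribute depends on where scanning takes place, which sections 6 and 10 leave unclear; behavioral and neurophysiological differences between Units remain possible either way.

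**What to change.** In sections 11 and 12:

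1. Form the development set from the first 38 FMD and first 38 HC of one Unit and the first 37 FMD and first 37 HC of the other. The remaining 75 + 75 are the test set. Name in advance which Unit supplies 38.
2. Call this a temporal validation, and report test performance overall and by Unit.
3. As a secondary analysis only, report leave-one-Unit-out performance in both directions as a check of transfer between the Units. The single algorithm taken to aims 2 and 3 stays the one from the stratified development set.
4. Reconcile the MRI location between section 6 and section 10.

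The cost is a slightly weaker validity claim and a few extra model fits. No subjects or study procedures are added, and the set sizes do not change.
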